#### Sample size

This project will implement the SISTAQUIT intervention in ACCHOs and Mainstream Health Services/sites. Sample size proposed is 10 of each health service or sites (N = 20), however if the demand is higher, we will aim to accommodate more services for the training, up to 30. With 20 sites, assuming an average of 8 HCPs trained per site are assessed for knowledge, attitudes and practices pre and post intervention, the study will have 90% power to detect a small to moderate standardised effect size of 0.2 standard deviations, with a 5% type 1 error rate.

### Intervention

Participating sites and their HCPs will have the option to choose one of the two iSISTAQUIT training packages available (Table 1).

**Table 1 pone.0274139.t001:** iSISTAQUIT package options.

Characteristics	Option 1: Evaluation-Research package (includes CPD points)	Option 2a: Training package with CPD points	Option 2b: Training Package without CPD points
iSISTAQUIT training	Yes	Yes	Yes
Research component	Yes	No	No
Surveys to complete	All surveys	Only pre- and immediate post-training HCP surveys acknowledged by HPMI as being done or not (irrespective of content) for CPD points	No surveys
Data collection	Medical practice software via Pen CS iSQ Topbar app (ABCD template) or Communicare iSQ clinical item (ABCD template)	None	None
Resources	Online training modules + treatment manual + patient flipchart + My journey booklet + NRT posters + ABCD desk mousepad + medical practice software templates + CO monitor/s + oral NRT	Online training modules + treatment manual + patient flipchart + My journey booklet	Online training modules + treatment manual + patient flipchart + My journey booklet
Option to get CPD points	Yes	Yes	No

ABCD: A-Ask/Assess, B- Brief Advice, C-Cessation, D- Discuss psychosocial context (of smoking)

CPD: Continued professional development

HPMI: Hunter Postgraduate Medical Institute

iSQ: iSISTAQUIT

#### Option 1. Evaluation research package

HCPs will be required to consent to completing the self-paced training modules, the reflective workbook and the pre- and post-training surveys (4 surveys in total). The training surveys will provide evidence on changes in knowledge, attitude and behaviours of the HCPs related to smoking cessation care. HCPs will be entered into a prize draw for completing all surveys and will have an option to claim CPD points.

The full iSISTAQUIT Evaluation-Research package consists, in addition to the training resources (treatment manual, patient flipchart and My Journey (patient) booklet), a) the provision of a carbon monoxide meter and oral nicotine replacement therapy (NRT), and, b) the choice of two medical practice software templates (Pen CS Topbar or Communicare) which aid and support the HCPs to enter the data about the patient’s medical consultation and the characteristics of the women’s quit attempts. The templates will be also utilised to guide the consultation according to the training using the ABCD approach [43]. ABCD approach stands for A—ask/assess; B—brief advice; C—cessation; and D—discuss the psychosocial context of smoking. This approach has been previously used in ICAN QUIT in Pregnancy and the SISTAQUIT RCT project.

#### Option 2. Training package

*Option 2a*. Training with professional or CPD points: HCPs complete the self-paced training modules and fill out the pre and immediate post training surveys. They also receive the treatment manual, patient’s flipchart and the My Journey (patient booklet). This option is suitable for HCPs that would like to do the training and obtain the professional or CPD points without participating in the research.

*Option 2b*. Training with no professional or CPD points: HCPs complete the self-paced training modules and receive the treatment manual, flipchart and My Journey patient booklet but do not complete the pre- and immediate post training surveys. This is for HCPs that do not want the professional or CPD points (for e.g. not a requirement in their profession) but would still like to get the benefits of the iSISTAQUIT training.

The two training schemes were introduced to cater to the capacity of the health services to be involved and the funder’s desire to increase services’ access to the program. Option 2 is offered to make the training equitably accessible to sites that otherwise would not be able to be involved in research due to the extra demands of the COVID-19 pandemic or other constraints.

For the rest of this paper, data collection and implementation of the study refers to services that choose option 1 (Evaluation-Research package), unless otherwise specified. Data from HCPs that choose option 2a will only be used for conferral of professional or CPD points and to calculate the program’s reach. Only data about reach will be collected from services that choose option 2b.

### Training delivery

Both training packages with the associated options will be available through the Moodle platform provided by the Hunter Postgraduate Medical Institute (HPMI). Moodle is a robust, secure, and integrated system learning platform for educators, administrators and learners. Moodle will be used for the associated training surveys (see https://moodle.com/security-privacy/) and participants will need to make an account to log into the HPMI website to access the online training and the surveys.

iSISTAQUIT training for both packages will have 14 e-Learning modules, taking approximately four hours to complete. The training will be internet-enabled and self-paced and includes videos, text, and interactive elements, supported by hardcopy resources i.e., the treatment manual and patient flipchart for HCPs and the My Journey (patient booklet), which includes augmented reality videos to aid smoking cessation care. The iSISTAQUIT e-Learning is designed to use the Eight Aboriginal Ways of Learning, is self-paced and accredited for professional development or CPD points with several professional colleges [44]. The Eight Aboriginal Ways of Learning involves using an Aboriginal pedagogy (such as story sharing, community links and symbols and images) and is congruent with the Australian Health Practitioner Regulation Agency (AHPRA) framework for cultural safe practice by HCP’s [44, 45].

### Site set-up

Consultations with and establishment of the Evaluation-Research sites will be completed by email, telephone and videoconference. The iSISTAQUIT Team will help facilitate the ethics processes and documentation required for the research collaboration. The team will also facilitate the provision of access to the electronic version of the iSISTAQUIT resources and to the e-Learning training via HPMI. Provision of hard copies of the iSISTAQUIT resources (patient booklets, flipcharts, treatment manuals), and provision of equipment (handheld Bedfont piCO Baby Carbon Monoxide Meter) and oral forms of NRT (with preference to those not currently subsidised on the Australian Pharmaceutical Benefit Scheme) will be facilitated by the team. Each service that chooses the full iSISTAQUIT Evaluation-Research package will be followed up by a site visit to support implementation, where feasible amid COVID19 restrictions. Geographic areas may be pragmatically selected for sequential roll out.

Services that opt for the iSISTAQUIT Training package, will similarly be established via the same communication channels, but will fill out a two-page registration form, giving details of their service and requirements. A communication log (CL) with the health services will be used to record the sites engaged, resources sent to them, potential participants, and information of the number of the annual number of pregnant women that reach the service.

#### Social media campaign

The research component of the social media campaign is being conducted from December 2021 to September 2022. After this date, the social media campaign may continue in a non-research capacity. The aims of the social media campaign are: to increase iSISTAQUIT brand recognition, increase awareness about smoking cessation for Aboriginal and Torres Strait Islander women in pregnancy, increase interest about the program and promote behaviour change among Aboriginal and Torres Strait Islander communities and health professionals. The creative approach for the social media campaign will be developed by the company Gilimbaa in partnership with IndigenousX who will be developing the social media strategy to deliver a comprehensive campaign. Gilimbaa and IndigenousX are Aboriginal owned and operated media, consultancy, and training organisations. This national campaign will consist of systematic advertising and promotion of iSISTAQUIT and video messages through various social media platforms that will be set-up, such as Facebook, Instagram, LinkedIn, and, Twitter. An Aboriginal owned company Ngakkan Nyaagu (NGNY) is developing an iSISTAQUIT website. The primary focus for distribution of the social media campaign will be through the early adopter service states namely Queensland, New South Wales, and South Australia. The ongoing management of the website and social media accounts will be led by Southern Cross University and will be updated regularly with advertising content such as professionally produced videos, photos, and posts.

*Video production*. Gilimbaa as the creative agency will conduct Community consultations (group discussions separately with Aboriginal and Torres Strait Islander women, health professionals and community leaders) to inform the creative approach and video content. Subject to pandemic and public health restrictions, it is anticipated that a series of short videos will be produced either in-house or in different locations across Australia, whichever is feasible. Key messaging in the videos will promote smoking cessation among Aboriginal and Torres Strait Islander women and families and highlight the importance of smoking cessation care, i.e., helping people and health practitioners feel confident and that it is worthwhile spending the time assisting pregnant women to quit. The videos will encourage Aboriginal and Torres Strait Islander women to seek and accept help from health providers, community, and family to quit smoking. A central Aboriginal talent will be engaged to present the iSISTAQUIT messages through short videos and bring to light community stories. Contingency plans will be made if the filming is interrupted due to travel restrictions.

### Outcome measures for iSISTAQUIT

#### Outcomes related to RE-AIM framework

This study will utilise the RE-AIM framework (Reach, Effectiveness, Adoption, Implementation and Maintenance) to plan, evaluate and report the intervention impact of the implementation of iSISTAQUIT (See Table 2). RE-AIM framework was chosen as it is a widely used implementation model that reports comprehensively on the key issues related to implementation studies- beginning with adoption and reach, followed by implementation and efficacy or effectiveness, and finishing with maintenance [46].

**Table 2 pone.0274139.t002:** RE-AIM framework evaluation.

RE-AIM component	Outcomes	Method of assessment (data sources)	Data sources
Reach	1. Service participation rate	• Number of HS participating in Evaluation-Research package / Number of HS approached (CL, RF) • Number of HS participating in Training only package/ number of HS approached (PTA, CCI)	• PenCS Topbar application or web-based version for iSISTAQUIT (ABCD template) or • Communicare iSISTAQUIT Clinical item (ABCD template)
	2. HCP participation rate	Number of HCP registered to do the training/ number of HCPs determined to be eligible to participate by the service (OM, RF)	
	3. Representativeness	Characteristics of HCPs such as age, sex and region of practice compared with national/regional figures available through national databases and peak bodies data (such as the General Practice Workforce providing Primary Care services in Australia)	Australian Government DOH General Practice Workforce providing Primary care services in Australia (https://hwd.health.gov.au/resources/data/gp-primarycare.html)
Effectiveness	1. Barriers and enablers	A 9 item, 5-point Likert scale (strongly disagree to strongly agree) questionnaire based on the Theoretical Domain Framework [49]. (OS)	• Online (through Moodle) pre-, immediate post- training and 3-month surveys
	2. Knowledge attitudes and practices related to SCC	Knowledge, Attitudes and Practices related to SCC measured through online pre-, immediate post- and 3 months post-training surveys. (OS)	• Online (through Moodle) pre-, immediate post- training and 3-month surveys
	3. Secondary outcomes	1. Smoking cessation rate: Percentage of women who change their smoking status (PTA, CCI) 2. Pregnant women participation rate: • Number of pregnant women who receive any iSISTAQUIT ABCD component/ number of eligible women seen by the service (PTA, CCI) • Number of pregnant women who receive My Journey booklet/ number of eligible women seen by the service (PTA,CL)	• PenCS Topbar application or web-based version for iSISTAQUIT (ABCD template) • Communicare iSISTAQUIT Clinical item (ABCD template) • Communicare iSISTAQUIT (smoking status) The ABCD tool includes a question that explores if the pregnant women quit smoking for at least 24 hours during the last 2 weeks, this question if available in the electronic medical records (PenCS Topbar application or web-based version for iSISTAQUIT or the Communicare iSISTAQUIT Clinical item). Additionally, a specific question regarding to the smoking status ‘do you smoke’ will be asked and recorded in Communicare. For all pregnant women that reported that they smoke, the status will be followed up and a percentage of the women that change of status reported by service.
Adoption	1. Practitioner participation rate	• Number of HCP who completed the training/ Number of HCPs who commenced the training (OM) (three separate rates calculated for HCPs who applied for CPD points, did not apply for CPD points and combined irrespective of CPD points). Rates will be compared statistically to determine if it’s worthwhile offering CPD points to improve uptake of training.	• Online (through Moodle, HPMI)
	2. Component adoption rate	• Four separate rates will be calculated for consultations in which A, B, C or D sections of the ABCD template were completed. This will be calculated by dividing number of respective completions (A, B, C or D) divided by number of consultations prompted by the app. The average component rate will be estimated for each component as the sum of the rates from each service divided by the number of participating services (PTA, CCI)	• PenCS Topbar application or web-based version for iSISTAQUIT (ABCD template) • Communicare iSISTAQUIT Clinical item (ABCD template)
Implementation	1. HCP iSISTAQUIT usage rate	• Number of HCP who used the iSISTAQUIT/ABCD template to engage women in smoking cessation care over the first 3 months /Number of HCP that commenced the training (OM, PTA, CCI) • Analysis of number and type of BCTs used from the template	• Online through Moodle, HPMI at 3 months and 6 months
Maintenance	1. Descriptive statistics (number and percentage)	• HCP’s/services that ask for more iSISTAQUIT resources (treatment manuals, patient flip charts, my journey booklets). (OS, AU) • HCPs that report iSQ training is a current part of their normal work. (OS) • HCPs that report iSQ training will become part of their normal work at 3 months post training. (OS) • Ongoing/long term use of the iSISTAQUIT ABCD template. (PTA, CCI) • Services interested in offering iSISTAQUIT training and resources (if available) to new HCPs joining the service after project completion. (QA)	• Qualitative analysis/audit of qualitative interviews by an external Aboriginal service. • The 3-month HCP survey. • Pen CS Topbar or Communicare de-identified aggregated quarterly data will provide iSISTAQUIT/ABCD template utilisation data until end of current study completion (31 December 2022). • End of study interviews

HS: health services; HCP: health care professional; ABS: Australian Bureau of Statistics.

CPD: Continued professional development; HPMI: Hunter Postgraduate Medical Institute; NRT: Nicotine Replacement therapy; iSQ: iSISTAQUIT

CL: Communication Log

RF: Registration form

RACGP: Royal Australian College of General Practitioners

PTA: Pen CS Topbar application

SCC: Smoking Cessation Care.

CCI: Communicare iSISTAQUIT Clinical Item

OS: Online Survey

QA: Quantitative analysis

AU: Audit

OM: Online through Moodle

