#### Status and timeline

The recruitment of sites has begun and to date 92 health providers have been enrolled and 42 health providers have completed training. Site recruitment will be completed by August 2022. All participating HCPs will complete training by October 2022. Data collection will be completed by November 2022. Data analysis and reporting of results will be completed by December 2022. The social media campaign was launched in December 2021 and evaluation completed by October 2022.

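### The Adoption rate is conditional on having started the training, so it cannot show uptake or an effect of CPD points on starting

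*Protocol article*

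**What the plan says.** All the definitions are in the protocol article, Table 2, under the heading on outcomes related to the RE-AIM framework.

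- **Reach, HCP participation rate:** "Number of HCP registered to do the training/ number of HCPs determined to be eligible to participate by the service".
- **Adoption, practitioner participation rate:** "Number of HCP who completed the training/ Number of HCPs who commenced the training (OM"). It is calculated for HCPs who applied for CPD points, for those who did not, and for both together. The rates are then compared statistically to decide whether it is "worthwhile offering CPD points to improve uptake of training".
- **Implementation, usage rate:** HCPs who used the template in the first 3 months, divided by "Number of HCP that commenced the training (OM, PTA, CCI").

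Registering and starting are separate events. Under Training delivery, "participants will need to make an account to log into the HPMI website to access the online training and the surveys", and the course itself is self-paced, with 14 modules taking about four hours.

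The only counts given are under Status and timeline: "to date 92 health providers have been enrolled and 42 health providers have completed training". The number who had commenced is not stated.

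**The concern.** Table 2 passes HCPs through three states (registered, commenced, completed) but forms rates from only two of the links: eligible to registered, and commenced to completed. An HCP who registers and never opens a module adds to the Reach numerator and is absent from the Adoption and usage denominators. No planned rate counts that HCP as not having taken up the training.

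This matters most for the decision written into the Adoption cell. Starting is part of taking up a self-paced course. A comparison restricted to starters can show whether CPD status goes with finishing, but not whether it goes with starting. If CPD points work mainly by getting registrants to begin, the planned comparison could find nothing, or could point the other way. The Conclusion says the results will inform a scale-up project, so a rate read as participation will carry weight.

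**Working it through.** **Inputs.** Rate definitions: Table 2. Counts: 92 enrolled and 42 completed, from Status and timeline. Not given: the number commenced, C. Table 2 states no planned value for any of these rates, so there is no figure to reproduce.

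**Step 1: relation between the two rates.** With R registered, C commenced and D completed,

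D/C = (D/R) × (R/C).

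Since C ≤ R, the planned rate D/C is never below the per-registrant rate D/R, and is strictly above it if any registrant has not started (given D > 0). The factor is R/C. The same factor separates usage per HCP commenced from usage per HCP registered.

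**Step 2: possible size.** Take enrolled to mean registered (an assumption), so R = 92 and D = 42. Then D/R = 42/92 = 45.7%. C must lie between 42 and 92, and the values below are assumed.

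| Commenced (assumed) | Planned rate D/C | Factor 92/C | Registered, not started (92 − C) | Started, not completed (C − 42) |
|---|---|---|---|---|
| 50 | 84.0% | 1.84 | 42 | 8 |
| 60 | 70.0% | 1.53 | 32 | 18 |
| 67 | 62.7% | 1.37 | 25 | 25 |
| 70 | 60.0% | 1.31 | 22 | 28 |
| 80 | 52.5% | 1.15 | 12 | 38 |
| 92 | 45.7% | 1.00 | 0 | 50 |

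The same 42 completers give very different planned rates, depending on a step that no planned rate measures. Non-starting is the larger of the two gaps only if fewer than 67 of the 92 had commenced.

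**Step 3: the CPD comparison.** Invented counts, to show what the definition can and cannot detect, with 46 registrants in each group:

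- *Case A.* CPD: 40 start, 28 finish. No CPD: 20 start, 14 finish. Per HCP commenced: 28/40 = 70% against 14/20 = 70%, no difference. Per HCP registered: 28/46 = 60.9% against 14/46 = 30.4%.
- *Case B.* CPD: 40 start, 26 finish. No CPD: 20 start, 16 finish. Per HCP commenced: 26/40 = 65% against 16/20 = 80%, favouring no CPD. Per HCP registered: 26/46 = 56.5% against 16/46 = 34.8%, favouring CPD.

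The planned comparison can therefore miss or reverse a difference in the share of registrants trained.

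**The case against.** **Completed/commenced is an ordinary completion rate, with both terms printed in full.** This stands. The rate is correct for what it computes. The fault is in titling it participation and using it to judge uptake.

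**The gap is not hidden.** The number registered is the Reach numerator and the number commenced is the Adoption denominator, and the Evaluation plan promises descriptive numbers as well as rates. A reader given both counts for the same HCPs could subtract them. So it would be wrong to infer that the step is invisible. It is only absent from every planned rate, and from the CPD comparison.

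**The interim figures prove little.** A reader might infer from 92 and 42 that failure to start is the largest loss. The document does not support this. The counts are a snapshot: site recruitment was to run to August 2022 and training to October 2022. The 50 who had not completed may be non-starters, drop-outs or HCPs still working through the modules. The 92 are not split by package, nor is enrolled said to mean registered.

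**Reach and Adoption are not meant to be multiplied.** A reader might infer that their product is offered as the share of eligible HCPs trained, and is overstated. The document makes no such claim. The Option 2 section says data collection refers to Option 1 unless otherwise specified, uses Option 2a data only for conferring points and for reach, and collects only reach data from Option 2b services. The two rates may cover different HCPs, so changing a denominator would not make the product valid unless both rates were restricted to the same packages.

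**Usage among HCPs who started is a reasonable implementation question.** This stands. A registrant denominator mixes not being exposed to the training with not using it, so it belongs beside the planned usage rate and not in its place.

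**The article condenses a fuller protocol.** That would answer a complaint about missing detail. Here the numerator, denominator and purpose of the comparison are all stated, and they do not match each other.

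**Conclusion.** The point holds as a mismatch between a stated definition and its stated use. Adoption as defined is conditional on starting, is higher than the per-registrant rate whenever a registrant does not start, and cannot show an effect of CPD points on starting. This follows from the definitions and needs no assumption about the data.

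The size cannot be determined. The interim per-registrant figure is 46%, if enrolled means registered and allowing for HCPs still in training. The planned rate would be 84%, 70% or 53% with 50, 60 or 80 commenced, and equal to 46% if all 92 had started. These are illustrations, not estimates of bias. The change is worth making because the plan already needs the counts and the choice alters what can be concluded about CPD points.

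**What to change.** In Table 2:

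1. Define the Adoption rate as completed/registered, overall and for the comparison by CPD status, with numerator and denominator drawn from the same HCP population and the packages covered named.
2. Report commenced/registered and completed/commenced as its two labelled components.
3. Keep template users/commenced as the usage rate and show template users/registered beside it, for Option 1 HCPs.

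The registered and commenced counts already feed planned rates, through Moodle and the registration form. One practical condition applies: CPD status must be known for HCPs who never start, so it has to be recorded at registration. The article does not say when it is recorded. Even then the comparison covers only what happens after registering. It does not show whether CPD points bring HCPs to register, and the groups remain self-selected.

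The cost is a few more table lines and a headline Adoption rate that will be less favourable if any registrants do not start.

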## Material and methods

iSISTAQUIT is a quasi-experimental, [41] multicentre, single arm implementation study aiming to implement evidence based culturally competent iSISTAQUIT training among health practitioners that provide support and assistance to pregnant Aboriginal and Torres Strait Islander women in Australia.

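### Comparing completion between HCPs who did and did not apply for CPD points cannot show whether offering points raises uptake

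*Protocol article*

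**What the plan says.** In the protocol article, section Outcomes related to RE-AIM framework, the first Adoption outcome in Table 2 divides the number of HCPs who finish the training by the number who start it. It asks for "three separate rates calculated for HCPs who applied for CPD points, did not apply for CPD points and combined irrespective of CPD points". It then states the purpose: "Rates will be compared statistically to determine if" it is "worthwhile offering CPD points to improve uptake of training".

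Other sections define who falls into these groups:

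- Material and methods describes a "multicentre, single arm implementation study".
- Intervention: "Participating sites and their HCPs will have the option to choose one of the two iSISTAQUIT training packages available".
- Option 1. Evaluation research package: "HCPs will be entered into a prize draw for completing all surveys and will have an option to claim CPD points".
- Option 2. Training package: 2a carries points. 2b is for HCPs who do not want them, with profession given as one example of a reason.
- The same section makes Option 1 the default scope for data collection in the rest of the article. It limits 2a data to awarding points and calculating reach, and adds: "Only data about reach will be collected from services that choose option 2b".

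Uptake in the sense of joining the training appears in the Reach rows of Table 2 as HCPs registered over HCPs eligible. That rate has no breakdown by CPD points.

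**The concern.** The article fixes the groups, the rate and the conclusion to be drawn, so this is not a detail left to an analysis plan. The conclusion concerns the effect of making an offer, but the comparison is between people who took up the offer and people who did not. HCPs who apply for points may differ from the others in profession, motivation and time, and any of these could affect whether they finish. The outcome is also finishing, while the question is about uptake.

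The Conclusion section says the results will inform a scale-up project. A difference in completion read as the effect of CPD points could be carried into that project as a reason to keep or drop them, without evidence for either.

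**Working it through.** The article gives no sample size, power or expected difference for this comparison, so there is no figure to reproduce. The check sets the sections side by side and then asks how large a gap could arise with no effect of the offer.

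**1. Does the offer vary?** Within Option 1, no: every HCP may claim points, so applicants and non-applicants have had the same offer. Across packages, 2b carries no points, but it is chosen and not assigned. No group is set up to go without the offer.

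**2. Does the rate measure uptake?** No. Its denominator is HCPs who have started, so all of them have already joined. Splitting the Reach rate by CPD application would not help either, because eligible HCPs who never register have no application status.

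**3. Which HCPs are counted?** The Adoption row names no package, so the Option 1 default applies. If 2a and 2b HCPs are meant to be included, the row conflicts with the data-use limits in Option 2. Training package.

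**4. Gap from self-selection alone.** The values in this step are assumptions. Let a share m of HCPs be more motivated. They complete with probability p1 and apply with probability a1; the rest do so with p2 and a2. Within each stratum, applying has no effect on completing.

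- Completion among applicants = [m·a1·p1 + (1−m)·a2·p2] / [m·a1 + (1−m)·a2]
- Completion among non-applicants: the same, with 1−a1 and 1−a2 in place of a1 and a2

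With m = 0.5:

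| p1 / p2 | a1 / a2 | Applicants | Non-applicants | Gap |
|---|---|---|---|---|
| 0.6 / 0.4 | 0.6 / 0.4 | (0.18+0.08)/0.5 = 52% | (0.12+0.12)/0.5 = 48% | 4 points |
| 0.7 / 0.3 | 0.7 / 0.3 | (0.245+0.045)/0.5 = 58% | (0.105+0.105)/0.5 = 42% | 16 points |
| 0.7 / 0.3 | 0.9 / 0.1 | (0.315+0.015)/0.5 = 66% | (0.035+0.135)/0.5 = 34% | 32 points |

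**5. Gap if application is recorded only at completion.** This timing is also an assumption. Status and timeline reports 92 HCPs enrolled and 42 finished so far (42/92 = 45.7%). Treat the 92 as starters, and let a fraction q of the 42 finishers claim points. Applicants then complete 100% by construction, and non-applicants complete (42 − 42q)/(92 − 42q):

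- q = 0.25: 31.5/81.5 = 38.7%
- q = 0.50: 21/71 = 29.6%
- q = 0.75: 10.5/60.5 = 17.4%

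The gaps are about 61, 70 and 83 points, all from the classification. The 42/92 is an interim count used only for illustration.

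**The case against.** Much can be said for the plan, and part of it stands.

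- **A significant result is not assured.** A reader might infer that a spurious significant difference is almost certain. That needs points to be claimed only on finishing, and the article does not say when they are claimed. Without that timing the gap may be small. Take 160 HCPs (the 20 sites of 8 in the Sample size section), split equally and ignoring clustering. Then 52% against 48% has standard error √[2(0.52×0.48)/80] = 0.079, z of about 0.5 and power of about 8%. For 58% against 42%, z is about 2.05 and power about 54%. This objection stands: a spurious gap is possible, and its size is unknown.
- **The comparison is not barred.** A reader might infer that the limits on Option 2 data make it impossible. They do not, because Option 1 contains both applicants and non-applicants. But within Option 1 the offer is the same for everyone, so its effect cannot be estimated there.
- **The combined rate.** Its listing might suggest a test of that rate against its own parts. Nothing in the article says so. The natural reading is applicants against non-applicants, with an overall rate beside them.
- **Loose use of the word uptake.** It might mean seeing the training through. That would soften the mismatch of outcome but leave the self-selection untouched.
- **Small role.** This is one process measure. The analysis of knowledge, attitudes and practices is unaffected, and no section makes a decision on CPD points depend on this comparison.

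**Conclusion.** The point holds in a limited form. The completion rates are legitimate descriptive results. The conclusion attached to them is not supported, for two reasons taken from the text alone: CPD status is self-chosen, with no variation in the offer under the default Option 1 scope, and the rate is conditional on having started.

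The size of any spurious gap cannot be known from the article. The range of about 4 to 32 points rests on assumed strata. The larger gaps of about 61 to 83 points rest on the further assumption that application is recorded at completion. The verdict depends on neither set of figures; they show only that a gap can appear when the offer does nothing. The text should be changed, but the consequence is confined to one Adoption outcome and what is said about CPD points.

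**What to change.** - In Table 2, delete the stated purpose of deciding whether offering points is worthwhile for uptake.
- Report completion among starters with 95% confidence intervals for the two non-overlapping groups (applied, did not apply), with the overall rate beside them. Label the results descriptive and non-causal.
- Where the information exists, classify HCPs by CPD intention or package recorded before training starts, so that finishing cannot determine group membership.
- State whether the Adoption rate covers Option 1 only. If Option 2 HCPs are meant to be included, reconcile the row with the data-use limits in Option 2. Training package. Those HCPs took a route outside the research, so any wider use of their data is subject to ethics approval and consent.

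The cost is a wording change in Table 2 and the loss of a causal claim about CPD points. Restricting the row to Option 1 needs no new data. Including Option 2 would carry the ethics and consent work as well.
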